**ENROLMENT**												
Eligibility screen	X											
Informed consent	X											
Allocation		X										
**INTERVENTIONS**												
SBRT fraction (arm A)					X	X	X					
Nivolumab q2w (arm A & B)			X	X				X	X	X		
**ASSESSMENTS**												
Demographics, medical Hx, performance status	X											
Imaging (CT or PET/CT)	X										X	
Fecal sample			X								X	
Liquid biopsy			X		X^c^			X				X
Adverse events			X	X	X^c^			X	X	X	X	X^d^
Quality of life			X									X^e^

*C* cycle; *CT* computed tomography; *D* day; *Hx* history; *PET* positron emission tomography; *q2w* 2-weekly; *SBRT* stereotactic body radiotherapy

^a^ SBRT is given on Wednesday-Friday-Monday or Friday-Monday-Wednesday, depending on whether nivolumab is administered on Tuesday or Thursday, respectively

^b^ Consultation after imaging; until disease progression as per iRECIST

^c^ Only for patients in study arm A

^d^ Until 3 months after radiotherapy

^e^ At least every 6 months

**Table 2 Tab2:** Study calendar for nivolumab 4-weekly: SBRT prior to C2; first evaluation after C3

	STUDY PERIOD									
	Enrolment	Allocation	Post-allocation						Close-out	Long-term follow-up
**TIMEPOINT**	**Pre-study**	**D-14 to -1**	**C1D1**	**C2D-6**	**C2D-4 or -3**^**a**^	**C2D-1**	**C2D1**	**C3D1**	**C3D +1 to +14**	**Every evaluation**^b^
**ENROLMENT**										
Eligibility screen	X									
Informed consent	X									
Allocation		X								
**INTERVENTIONS**										
SBRT fraction (arm A)				X	X	X				
Nivolumab q4w (arm A & B)			X				X	X		
**ASSESSMENTS**										
Demographics, medical Hx, performance status	X									
Imaging (CT or PET/CT)	X								X	
Fecal sample			X						X	
Liquid biopsy			X	X^c^			X			X
Adverse events			X	X^c^			X	X	X	X^d^
Quality of life			X							X^e^

*C* cycle; *CT* computed tomography; *D* day; *Hx* history; *PET* positron emission tomography; *q4w* 4-*weekly SBRT* stereotactic body radiotherapy

^a^ SBRT is given on Wednesday-Friday-Monday or Friday-Monday-Wednesday, depending on whether nivolumab is administered on Tuesday or Thursday, respectively

^b^ Consultation after imaging; until disease progression as per iRECIST

^c^ Only for patients in study arm A

^d^ Until 3 months after radiotherapy

^e^ At least every 6 months

**Table 3 Tab3:** Study calendar for pembrolizumab or atezolizumab 3-weekly: SBRT prior to C3; first evaluation after C4

	STUDY PERIOD										
	Enrolment	Allocation	Post-allocation							Close-out	Long-term follow-up
**TIMEPOINT**	**Pre-study**	**D-14 to -1**	**C1D1**	**C2D1**	**C3D-6**	**C3D-4 or -3**^**a**^	**C3D-1**	**C3D1**	**C4D1**	**C4D +5 to +20**	**Every evaluation**^b^
**ENROLMENT**											
Eligibility screen	X										
Informed consent	X										
Allocation		X									
**INTERVENTIONS**											
SBRT fraction (arm A)					X	X	X				
Pembrolizumab or atezolizumab q3w (arm A & B)			X	X				X	X		
**ASSESSMENTS**											
Demographics, medical Hx, performance status	X										
Imaging (CT or PET/CT)	X									X	
Fecal sample			X							X	
Liquid biopsy			X		X^c^			X			X
Adverse events			X	X	X^c^			X	X	X	X^d^
Quality of life			X								X^e^

*C* cycle; *CT* computed tomography; *D* day; *Hx* history; *PET* positron emission tomography; *q3w* `3-weekly; *SBRT* stereotactic body radiotherapy

^a^ SBRT is given on Wednesday-Friday-Monday or Friday-Monday-Wednesday, depending on whether pembrolizumab/atezolizumab is administered on Tuesday or Thursday, respectively

^b^ Consultation after imaging; until disease progression as per iRECIST

^c^ Only for patients in study arm A

^d^ Until 3 months after radiotherapy

^e^ At least every 6 months

## Statistical analysis

### Sample size

This trial is designed to assess whether SBRT to maximum 3 lesions after 2 cycles of CPIs could prolong PFS as compared to standard of care in metastatic patients. The study has a two-sided 0.05% type I error and 80% power to detect an improvement in PFS of 3 months in the intervention group as compared to the control group using a stratified log-rank test. Median PFS for the control arm was estimated at 3.1 months. Median PFS after initiation of CPIs is approximately as follows:
20% metastatic melanoma (1st-3rd line): 5.2 months [1, 4, 24–26]20% renal cell carcinoma (2nd line): 4.6 months [27]20% non-small cell lung carcinoma (2nd-3rd line): 2.7 months [3, 28, 29]25% bladder cancer (1st-3rd line): 2.2 months [2, 30]15% head- and neck cancer (1st-2nd line): 2.0 months [31, 32]

We estimate to recruit 30% oligometastatic patients (defined as ≤3 metastases) and 70% non-oligometastatic (defined as > 3 metastases) in the trial. We hypothesize that an improved PFS of 3 months will be seen. We chose for a 36 month accrual time and a 12 month follow-up time. Analysis is planned 9 months after inclusion of the last patient.

Using these assumptions and including a 5% at random dropout rate, the trial requires a total of 98 patients to be randomized in to two groups. Sample size calculation was performed using R version 3.4.1.

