#### Evaluation and randomization

Patients must be restaged within 4 weeks prior to randomization. The study will employ a 1:1 randomization between arm A: arm B, stratified on primary tumor histology (melanoma, renal cell carcinoma, non-small-cell carcinoma, urothelial carcinoma or head-and-neck squamous cell carcinoma) and on the number of metastases present at the time of inclusion (≤3 or > 3). Randomly permutated blocks of variable length 2 and 4 will thus be assigned to each stratum. Within each block, assignment to treatment and control is random but balanced. Every patient is assigned a treatment arm following the randomization-scheme. As this is an open-label trial, the randomization procedure and outcome will not be blinded.

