### Data analysis and monitoring

Patients will be analyzed according to the group to which they were assigned (intention-to-treat). Descriptive statistics will be used to summarize patient characteristics per treatment group.

PFS will be defined as the time from randomization to disease progression (as per iRECIST using CT or PET/CT) or death from any cause. PFS will be compared between groups using the stratified log-rank test. Kaplan-Meier estimates of 1-year PFS and OS will be provided for each treatment group and as a post-hoc subgroup analysis based on patient characteristics described above. Median follow-up time will be derived using both complete and incomplete follow-up times. Cox proportional hazards regression will be used to provide hazard ratio estimates when assessing PFS using covariates of interests. A *p*-value of less than 0.05 will be considered statistically significant.

For the evaluation of biomarkers on one time point, differences between groups will be tested using the Mann-Whitney U test. For the evaluation of biomarkers over time, differences between groups will be tested using the Wilcoxon signed-rank test. To evaluate correlations, Spearman correlation coefficients will be calculated. A p-value of less than 0.05 will be considered statistically significant.

All statistical analyses will be performed using SPSS (SPSS Inc., Chicago, Il, USA). RNA sequencing data will be analyzed using dedicated pipelines. Further processing of the count tables will be performed in R (v.3.5.1).

In order to avoid introducing bias no interim analysis will be performed. Early trial termination may be deemed necessary in case of poor accrual. As the experimental treatment carries minimal risks, no data monitoring committee will be implemented, nor will there be a predefined stopping procedure.

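### The Sample size section states a two-sided type I error of 0.05%, which contradicts the p < 0.05 threshold of the analysis section; 98 patients fit 5%, not 0.05% (a unit error, minor)

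*Protocol article*

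**What the plan says.** The Sample size section gives the design characteristics of the primary comparison: "The study has a two-sided 0.05% type I error and 80% power to detect an improvement in PFS of 3 months". The effect is set by two further sentences: "Median PFS for the control arm was estimated at 3.1 months", and "We hypothesize that an improved PFS of 3 months will be seen". With 5% random dropout allowed for, the section arrives at 98 randomized patients.

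The section on data analysis and monitoring names the test: "PFS will be compared between groups using the stratified log-rank test". In the same paragraph it sets the cut-off for the p-value: a "value of less than 0.05 will be considered statistically significant". It also states that there will be no interim analysis, and it describes no adjustment for multiple testing.

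Under Evaluation and randomization, the design has two stratification factors: "The study will employ a 1:1 randomization between arm A: arm B, stratified on primary tumor histology" (five types), together with the number of metastases at two levels. Crossing them gives 10 strata.

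**The concern.** A level of 0.05% is alpha = 0.0005. A threshold of 0.05 is alpha = 5%. The two sections describe the same primary test, and they differ by a factor of 100 with no reason given. Alpha is one of the few figures a reader needs to check the sample size and to know what counts as a positive result, and the article states it in two incompatible ways. Anyone who tries to reproduce the 98 patients from the Sample size section as printed will fail. This is also not detail that the article leaves to another document, because the article prints the value.

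**Working it through.** **Inputs from the protocol article.** Control median PFS 3.1 months; gain 3 months, so 6.1 months in the SBRT arm; power 80%; 1:1 allocation; accrual 36 months; follow-up of 12 months, with analysis 9 months after the last inclusion (both were tried); dropout 5%; five histologies in proportions 20/20/20/25/15%; disease burden 30/70%; blocks of 2 and 4; N = 98.

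**Assumptions not in the article.** Exponential PFS, uniform accrual, and the same median in both burden strata within a histology. The implied hazard ratio is then 3.1/6.1 = 0.508, with ln(0.508) = -0.677.

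**Step 1: can the stated 98 be reproduced at 5%?** Schoenfeld's formula for an unstratified log-rank test is events = 4(z_alpha/2 + z_power)² / (ln HR)².

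- Two-sided 5%: 4(1.960 + 0.842)² / 0.458 = 68.5, so 69 events. That is 76 to 77 patients after dropout.
- Freedman's formula gives 74 events and 82 to 84 patients.

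Both fall short of 98. The planned test, however, is stratified over 10 cells, some of them very small: the expected size of the head and neck stratum with at most 3 metastases is 0.15 × 0.30 × 98 = 4.4 patients. Such cells lose information. Simulating the stratified test with 93 evaluable patients, permuted blocks and analysis at 9 months (10,000 replicates, error about 0.5 percentage points) gives:

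| PFS model | Mean events | Power at 5% | Power at 0.05% |
|---|---|---|---|
| Same medians (3.1 vs 6.1) in all strata | 88.2 | 80.7% | 24.4% |
| Histology-specific medians, common hazard ratio 0.508 | 87.0 | 80.3% | 24.2% |
| Histology-specific medians, 3 months added | 87.4 | 81.9% | 25.6% |

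With 12 months of follow-up, the first row becomes 80.5% and 24.5%. Inflating for dropout, 93/0.95 = 97.9, so 98. The stated sample size is reproduced at two-sided 5%.

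**Step 2: the same design at 0.05%.** The last column gives about 25%. If all 98 patients enter and dropouts are censored, power is 26% to 27%. A check without simulation agrees: a normal-theory test with exactly 80% power at two-sided 0.05 has power Φ(1.960 + 0.842 - 3.481) = Φ(-0.679) = 25% at two-sided 0.0005.

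**Step 3: spread over methods at 0.05%.** Unstratified Schoenfeld with 88 to 95 events gives 38% to 43%. For example, with 88.3 events, √(88.3/4) × 0.677 - 3.481 = -0.30 and Φ(-0.30) = 38%. Freedman gives 34% to 38%. The full range is about 24% to 43%.

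**Step 4: what 0.05% would require.** Schoenfeld: 4(3.481 + 0.842)² / 0.458 = 163.1, so 164 events, more than the 98 patients in the trial. With the stratified test, about 200 patients give 80% power in simulation.

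**The case against.** The strongest reply is that 0.05% is plainly a slip for 0.05 or 5%, that the only explicit decision rule is the p < 0.05 of the analysis section, and that nothing in the trial depends on the misprint. Most of this stands. It is why the point is graded as minor, but it does not make the printed figure right.

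Three stronger readings are tempting, and the article does not support them.

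- A reader might infer that the trial is underpowered. That holds only if the test were actually run at 0.0005, and the analysis section says otherwise.
- A reader might put the power at 0.05% at about 40%. That figure comes from the unstratified Schoenfeld formula, which gives 89% to 91% power at 5% and so does not match the article's 80%. The test that reproduces 98 gives about 25%.
- A reader might say that 98 patients are compatible with 5% alone. This goes too far. By the unstratified formula, 80% power with 88 to 93 events corresponds to a two-sided alpha of roughly 1.5% to 2%. The match at 5% depends on simulating the stratified test under assumptions that the article does not state; for the method, it says only that R was used. The data support the weaker statement: consistent with 5%, inconsistent with 0.05%.

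**Conclusion.** The type I error in the Sample size section is wrong as printed. It contradicts the significance threshold of the analysis section by a factor of 100, and it cannot give 80% power with 98 patients: power would be about 25% with the planned test, and no more than about 43% by any method tried. At two-sided 5% the planned test has about 80% power with 93 evaluable patients, which is 98 after dropout. The contradiction is certain from the text. The power figures rest on exponential PFS, uniform accrual and equal medians across burden strata within a histology, but the conclusion that 0.05% does not fit holds under every variant examined. The consequence is confined to reporting: a unit error, with the design and the planned test unaffected. It is a minor item that should be fixed.

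**What to change.** In the Sample size section, replace the stated level with a two-sided 5% (alpha = 0.05) type I error, so that it agrees with the threshold under Data analysis and monitoring. If the full protocol or analysis plan carries the same figure, correct it there too. The cost is a few words: N = 98, the stratified log-rank test and the conduct of the trial do not change. Adding the implied hazard ratio of about 0.51 would help a reader check the calculation, but it is optional and the correction does not depend on it.

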### Data analysis and monitoring

Patients will be analyzed according to the group to which they were assigned (intention-to-treat). Descriptive statistics will be used to summarize patient characteristics per treatment group.

PFS will be defined as the time from randomization to disease progression (as per iRECIST using CT or PET/CT) or death from any cause. PFS will be compared between groups using the stratified log-rank test. Kaplan-Meier estimates of 1-year PFS and OS will be provided for each treatment group and as a post-hoc subgroup analysis based on patient characteristics described above. Median follow-up time will be derived using both complete and incomplete follow-up times. Cox proportional hazards regression will be used to provide hazard ratio estimates when assessing PFS using covariates of interests. A *p*-value of less than 0.05 will be considered statistically significant.

For the evaluation of biomarkers on one time point, differences between groups will be tested using the Mann-Whitney U test. For the evaluation of biomarkers over time, differences between groups will be tested using the Wilcoxon signed-rank test. To evaluate correlations, Spearman correlation coefficients will be calculated. A p-value of less than 0.05 will be considered statistically significant.

All statistical analyses will be performed using SPSS (SPSS Inc., Chicago, Il, USA). RNA sequencing data will be analyzed using dedicated pipelines. Further processing of the count tables will be performed in R (v.3.5.1).

In order to avoid introducing bias no interim analysis will be performed. Early trial termination may be deemed necessary in case of poor accrual. As the experimental treatment carries minimal risks, no data monitoring committee will be implemented, nor will there be a predefined stopping procedure.

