### Objectives

Primary endpoint:
Progression-free survival (PFS) will be analyzed in all patients who received at least one cycle of CPIs. PFS is defined as the time from randomization to disease progression or death from any cause. Disease progression will be evaluated using systemic imaging by computed tomography (CT) or positron emission tomography (PET) CT and will be defined according to immune Response Evaluation Criteria in Solid Tumors (iRECIST) [20]. Imaging will occur every 3 months, or earlier if clinically indicated.Secondary endpoints:
Overall survival (OS) is defined as the time from trial randomization to the date of death from any cause.Best objective overall response as per iRECIST and RECIST 1.1 [21].Local control of the irradiated lesion(s) will be assessed per RECIST 1.1.Adverse events will be scored using the Common Terminology Criteria for Adverse Events (CTCAE) version 5.0.Quality of life (QOL) scoring using the EORTC QLQ-C30. Raw scores will be transformed to a linear scale ranging from 0 to 100. The results will be presented in accordance with the most recent guidelines for reporting health related QOL randomized controlled trials.Systemic responses during the trial will be assessed using peripheral blood samples. Using flow cytometry, subsets of immune cells, selected immune checkpoints and cell death markers will be identified. Cytokines will be measured via multiplex analysis. Cell-free DNA will be analyzed using shallow whole genome sequencing which will allow reliable non-invasive copy-number profiling, as previously demonstrated by our group [22]. In addition, germline DNA and circulating extracellular RNA will be analyzed. If at any point prior to or during the study, tissue samples of the primary tumor or metastatic foci were obtained from the trial patient for diagnostic purposes and stored, any remaining tissue may be retrieved from the respective pathology department. Analyses of this formalin-fixed paraffin embedded (FFPE) material will include isolation of tumor RNA and DNA, programmed death-ligand 1 (PD-L1) expression and tumor infiltrating lymphocytes (TIL). Depending on the published scientific literature available at the time of data cut off, additional analyses could be performed.The predictive and prognostic value of the composition of the gut microbiome will be assessed using a serial fecal sampling.

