#### Study calendar

Baseline/pre-study evaluations:
Documentation of the patient’s medical history and all medicationRegistration of baseline symptoms/toxicity and QOLKarnofsky Performance statusClinical examinationBlood draw assessing at least the following elements: complete blood count (hemoglobin, white blood cell count and formula, thrombocyte count), electrolytes (sodium, potassium), renal function (creatinine, blood urea nitrogen), liver function (alanine aminotransferase, aspartate aminotransferase, gamma-glutamyltransferase, alkaline phosphatase), lactate dehydrogenase and C-reactive protein.

Baseline evaluations are to be conducted within 2 weeks prior to start of checkpoint inhibitors.

During study:
Registration of symptoms before first cycle of checkpoint inhibitors, at start of radiotherapy and at end of radiotherapy (if applicable) and at least every 4 weeks until 4 months after randomization. Toxicity will be assessed using the CTCAE version 5.0.QOL will be assessed at baseline, at first evaluation and every 6 months thereafter. QOL will be assessed using the QLQ-C30 questionnaire.A fecal sample will be obtained prior to start of CPI treatment and at the first evaluation.Blood samples (EDTA and serum) for immunological analysis will be obtained prior to start of CPIs, before first fraction (Arm A), before the second/third cycle of CPIs and at every evaluation (consultation after imaging) as long as patient receives CPI (i.e. liquid biopsy).Patients will be followed up until disease progression defined as per iRECIST.Off-study and follow-up evaluationsOnce a subject experiences confirmed disease progression, the subject moves into the survival follow-up phase and should be contacted by telephone every 12 weeks to assess for survival status until death, withdrawal of consent or the end of the study, whichever occurs first.Monitoring of progression and survival.

Study calendars for different CPI treatment schedules are represented in Tables 1, 2, and 3.

**Table 1 Tab1:** Study calendar for nivolumab 2-weekly: SBRT prior to C3; first evaluation after C5

	STUDY PERIOD											
	Enrolment	Allocation	Post-allocation								Close-out	Long-term follow-up
**TIMEPOINT**	**Pre-study**	**D-14 to -1**	**C1D1**	**C2D1**	**C3D-6**	**C3D-4 or -3**^**a**^	**C3D-1**	**C3D1**	**C4D1**	**C5D1**	**C5D +1 to +14**	**Every evaluation**^b^

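### Follow-up blood and fecal markers are compared between arms without the pre-CPI value sampled in both arms: a valid test, but less precise than the planned samples allow

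*Protocol article*

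**What the plan says.** The protocol article, under Data analysis and monitoring, has two sentences on biomarker comparisons. For a single time point: "For the evaluation of biomarkers on one time point, differences between groups will be tested using the Mann-Whitney U test". For changes: "For the evaluation of biomarkers over time, differences between groups will be tested using the Wilcoxon signed-rank test". Neither mentions adjustment for a pre-treatment value. The significance rule follows: "To evaluate correlations, Spearman correlation coefficients will be calculated. A p-value of less than 0.05 will be considered statistically significant".

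The Study calendar section sets the sampling. For blood: "Blood samples (EDTA and serum) for immunological analysis will be obtained prior to start of CPIs", then again before the second or third cycle and at each evaluation while the patient is on CPI. For stool: "A fecal sample will be obtained prior to start of CPI treatment and at the first evaluation". In Tables 1 to 3 the C1D1 liquid biopsy and fecal sample carry no arm restriction. Among the biomarker samples, the footnote "Only for patients in study arm A" is attached only to the blood draw before the first SBRT fraction.

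Not every marker has a before/after pair. The Objectives section also lists germline DNA, and stored diagnostic tissue of which "any remaining tissue may be retrieved from the respective pathology department".

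**The concern.** Immune-cell subsets, cytokines and microbiome measures can be expected to differ between patients before any treatment, the more so in a trial that mixes five histologies and several treatment lines. A test on the follow-up value alone leaves that variation in the comparison as noise. If a patient's follow-up value is correlated with the pre-CPI value, part of the noise can be removed with samples the trial already plans to take.

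The systemic immune response and the microbiome are listed as secondary endpoints, and the abstract says the trial will inform on the immunological impact of SBRT. With at most 49 patients per arm, and fewer where later samples depend on continued CPI treatment, avoidable imprecision could hide a moderate effect.

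**Working it through.** **Is a baseline available in both arms?** Yes. The Study calendar text and Tables 1 to 3 plan pre-CPI blood and stool for all patients. Blood is repeated in both arms before cycle 2 or 3 and at evaluations, and stool at the first evaluation.

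**Does another planned test use it between arms?** No. A signed-rank test works on paired differences within patients. It can show that a marker changed within one arm, but not that the change differs between two independent arms.

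**Inputs.** The sample size section says "the trial requires a total of 98 patients to be randomized in to two groups", and allocation is 1:1, so n = 98/2 = 49 per arm. Alpha is 0.05, taken as two-sided. The article gives no biomarker effect size, SD, correlation or power, so there is no planned figure to reproduce; the total of 98 was set for PFS. Assumed here: a shift d of 0.5 SD, approximately normal values (on a log scale if need be), and a baseline/follow-up correlation ρ from 0.3 to 0.8.

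**Formulas.** The efficiency of rank tests under normality is 3/π = 0.955.

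- Follow-up value only: power = Φ(d·√(0.955·n/2) − 1.96).
- Baseline-adjusted: residual SD is √(1−ρ²), so d is replaced by d/√(1−ρ²).
- Change score: SD is √(2(1−ρ)), so d is replaced by d/√(2(1−ρ)).

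**Unadjusted.** √(0.955 × 49/2) = √23.40 = 4.837. Then 0.5 × 4.837 = 2.419, 2.419 − 1.96 = 0.459, and Φ(0.459) = 0.68.

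**Adjusted, example at ρ = 0.5.** 2.419/√0.75 = 2.793, 2.793 − 1.96 = 0.833, and Φ(0.833) = 0.80.

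| ρ (assumed) | 1−ρ² | Follow-up only | Baseline-adjusted | Gain, points | Simulated rank ANCOVA | Mann-Whitney on change |
|---|---|---|---|---|---|---|
| 0.3 | 0.91 | 68% | 72% | 4 | 71% | 53% |
| 0.5 | 0.75 | 68% | 80% | 12 | 77% | 68% |
| 0.6 | 0.64 | 68% | 86% | 18 | 84% | 77% |
| 0.7 | 0.51 | 68% | 92% | 25 | 90% | 88% |
| 0.8 | 0.36 | 68% | 98% | 30 | 97% | 97% |

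The simulated rank analysis of covariance runs 1 to 3 points below the formula. The share of information left unused is ρ²: 9%, 25%, 36%, 49% and 64%.

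**Sensitivity.**

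- 35 per arm, 0.5 SD: 53% unadjusted against 57%, 66%, 72%, 82% and 93%.
- 49 per arm, 0.3 SD: 31% against 33%, 39%, 44%, 53% and 68%.
- 49 per arm, 0.8 SD: already 97% unadjusted, so little is left to gain.

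**Validity.** Simulated type I error of the Mann-Whitney test was 0.04 to 0.06, in line with the nominal 0.05.

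**The case against.** The strongest reply is that an unadjusted rank test for many exploratory markers is a conventional choice with few assumptions, that these are secondary translational endpoints with no power target, and that nothing here is miscalculated. This stands as far as it goes: the point concerns efficiency, not error.

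The text is also broader than post-baseline arm comparisons. It does not limit the single time point to follow-up samples, and it does not say that the groups are the arms. Arms is the natural reading, since the same section uses the word for treatment groups, but the biomarker aims could also involve outcome groups. Mann-Whitney suits those, baseline comparisons, and markers with no planned pair such as stored tissue and germline DNA. The point is confined accordingly.

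A third reply is that the over-time sentence already uses each patient's earlier value. It does, but through a paired test that gives no between-arm comparison. Correcting that sentence would help, and correcting it to baseline adjustment would resolve both problems. Correcting it to a plain change score would not: at a correlation of 0.3 the change score does worse than the follow-up value alone (53% against 68%), and at 0.5 it only equals it. By 0.7 the gap to full adjustment is small (88% against 92%).

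A reader might infer that most of the power is thrown away. The documents do not support this, because they give no correlation and no effect size. A reader might also infer that a chance baseline imbalance biases the test. In a given trial such an imbalance does shift the observed difference, but over randomisations the test keeps its error rate.

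**Conclusion.** The point holds as a loss of precision in between-arm comparisons of post-baseline blood and fecal markers. The named test ignores a pre-CPI value planned in both arms, and no other named test brings that value into a comparison of arms. For a 0.5 SD effect with 49 per arm, the cost is about 4 power points at a correlation of 0.3 and about 30 at 0.8 (slightly less by simulation). It becomes substantial only from about 0.5 upwards, and it is small for effects near 0.8 SD. All of this rests on an assumed effect, assumed correlations and approximate normality. The documents do not support a reading that the test is invalid or biased, or that the loss is known to be large. The primary PFS analysis is not affected. A change is worth making because it needs no new data, and it belongs with the correction of the neighbouring signed-rank sentence.

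**What to change.** Revise the two biomarker sentences under Data analysis and monitoring together:

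- For between-arm comparisons of post-baseline markers that have a pre-CPI sample, use rank analysis of covariance, or a linear model on the log value, with arm and the patient's pre-CPI value as covariates.
- Do not use plain change scores for this purpose, since they lose power below a correlation of 0.5.
- Keep Mann-Whitney for baseline comparisons and for markers without a before/after pair.
- Keep the signed-rank test only to describe change within an arm.
- State what happens when the pre-CPI sample is missing.

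The cost is analysis wording only, with no extra samples, visits or patients. The downside is that patients without a pre-CPI sample need a missing-baseline rule, such as an indicator, or drop out of that marker's test.
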